**Methods and analysis:**

This will be a prospective, large sample, multicentre, randomised, controlled trial. Registration date is 1 December 2016. Actual study start date is 6 February 2017. Estimated study completion date is June 2020. A cohort of over 720 patients with inguinal hernias will be recruited from nine institutions in Liaoning Province, China. Patient randomisation will be stratified by centre to undergo inguinal hernia repair via the anterior transversalis fascia approach or the preperitoneal approach. Primary and secondary outcome assessments will be performed at baseline (prior to surgery), predischarge and at postoperative 1 week, 1 month, 3 months, 1 year and 2 years. The primary outcome is the incidence of postoperative chronic inguinal pain. The secondary outcome is postoperative complications (including rates of wound infection, haematoma, seroma and hernia recurrence).

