### Follow-up

Visit 3 (1 week after surgery via clinic visit or telephone follow-up)36-Item Short Form Health Survey (SF-36) score;Medical costs;Hernia recurrence (date and severity of recurrence). Recurrence will be diagnosed by the medical institutions, after being alerted by patients that symptoms are present.Presence or absence of haematoma and/or seroma;Wound infection (date and severity of wound infection).

Visit 4 (1 month after surgery via clinic visit or telephone follow-up)SF-36 score;Medical costs;Hernia recurrence (date and severity of recurrence). Recurrence will be diagnosed by the medical institutions, after being alerted by patients that symptoms are present.Presence or absence of haematoma and/or seroma;Wound infection (date and severity of wound infection).

Visit 5 (3 months after surgery via clinic visit or telephone follow-up)SF-36 score;Medical costs;Hernia recurrence (date and severity of recurrence). Recurrence will be diagnosed by the medical institutions, after being alerted by patients that symptoms are present.Presence or absence of haematoma and/or seroma;Wound infection (date and severity of wound infection).

Visit 6 (1 year after surgery via telephone follow-up)VAS pain score;SF-36 score;Medical costs;Hernia recurrence (date and severity of recurrence). Recurrence will be diagnosed by the medical institutions, after being alerted by patients that symptoms are present;Presence or absence of haematoma and/or seroma;Wound infection (date and severity of wound infection).

Visit 7 (2 years after surgery via telephone follow-up)VAS pain score;SF-36 score;Medical costs;Hernia recurrence (date and severity of recurrence). Recurrence will be diagnosed by the medical institutions, after being alerted by patients that symptoms are present;Presence or absence of haematoma and/or seroma;Wound infection (date and severity of wound infection).

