#### Secondary outcome measures

Postoperative complications including wound infection, rates of haematoma, seroma, hernia recurrence, intestinal obstruction, intestinal fistula, entocele, mesenteric thrombosis, femoral vein thrombosis, ischaemic orchitis, painful ejaculation, varicocele and scrotal oedema at postoperative 1 week, 1 and 3 months and 1 and 2 years.

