### AE reporting

Reporting time limit for AE will be within 24 hours of onset. In the clinical research period (from the time of signing informed consent to 1–2 years postoperatively), any AE occurring in any patient who received either surgical approach will be properly treated. According to the requirements of this study protocol and clinical evaluation, researchers will fill in the table of Adverse Events After Herniorrhaphy and submit this within 24 hours to the Clinical Research Center of Abdominal Wall Hernia, the Fourth Affiliated Hospital of China Medical University, China.

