### Patient completion/withdrawal from clinical study

Patients for whom the whole clinical data of at least 1 year are collected will be considered as complete cases. Patients with any one or more of the following criteria will be considered withdrawn from the study: mistakenly recruited, withdrawal of informed consent, on the request of the sponsor for safety reasons or patient conflicts or lost to follow-up. The date and reasons for withdrawal will be recorded on the eCRF. After termination of the study, the data collected at the last visit will be evaluated, except for data from those lost to follow-up.

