### Statistical analysis

Statistical analysis will be performed by a statician using SPSS V.19.0 software (SPSS). Continuous variables will be statistically described using the mean, SD, median, minimum and maximum. The categorical variables will be expressed using numbers and percentages.

The analysis will be performed on the basis of the intention-to-treat principle. Descriptive statistics of baseline information will be performed. The χ^2^ test or Fisher's exact test will be used for analysis of categorical variables, such as the incidence of postoperative chronic pain (primary outcome measure) and the incidence of postoperative complications (secondary outcome measure) between groups. Independent sample t-test or Mann-Whitney U test will be used for comparisons of continuous variables, such as SF-36 score, between groups. Cost-utility analysis will be used for economic evaluation, and sensitivity analysis of cost and utility will be performed.

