### Sample size

According to previous reports,^22 23^ we hypothesised that the incidence of chronic inguinal pain after anterior transversalis fascia repair and preperitoneal space approach was 10% and 3.4%, respectively. Taking α=0.05 and power=90%, the final effective sample size of n=600 was calculated. Assuming a patient loss rate of 20%, we require 720 patients.

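### Hernia recurrence to 2 years is compared as a crude proportion although follow-up is unequal by the plan's own terms; a time-to-event analysis of the recorded dates fits better

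*Protocol article*

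**What the plan says.** All references are to the protocol article.

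- **Outcome.** The secondary outcome section lists complications, hernia recurrence among them, ending with "varicocele and scrotal oedema at postoperative 1 week, 1 and 3 months and 1 and 2 years".
- **Test.** The statistical analysis section applies a chi-square or Fisher's exact test to "the incidence of postoperative complications (secondary outcome measure) between groups" and adds: "The analysis will be performed on the basis of the intention-to-treat principle". It names no method that uses observation time.
- **Dates.** At every follow-up visit the form records "Hernia recurrence (date and severity of recurrence").
- **Length of observation.** The AE reporting section gives the clinical research period as "from the time of signing informed consent to 1–2 years postoperatively". The completion/withdrawal section says: "Patients for whom the whole clinical data of at least 1 year are collected will be considered as complete cases". It also says that last-visit data are evaluated once the study ends, apart from those of patients lost to follow-up.
- **Loss.** The sample size section says: "Assuming a patient loss rate of 20%, we require 720 patients".
- **Calendar.** The abstract says: "Actual study start date is 6 February 2017". The end of the ethical approval section expects recruitment to finish in December 2019 and data collection in June 2020. The study completion section instead ends the study at the last participant's last visit.

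**The concern.** Recurrence can occur at any time over the 2 years. A simple proportion gives each patient one full unit of denominator, so a man seen recurrence-free for 8 months counts the same as one seen recurrence-free for 24. Where many patients cannot be observed for 24 months, the figure reported as a 2-year rate covers a shorter period.

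At stake are the absolute 2-year recurrence rates, which readers will compare with other series, and the size of the difference between arms. The information needed to avoid the problem, the date of recurrence, is collected and then not used by the stated test.

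**Working it through.** **The plan's own figure.** The plan gives no recurrence rate, so there is none to reproduce. Its effective sample size, for chronic pain at 10% versus 3.4%, does reproduce with two-sided α = 0.05, 90% power and 1:1 allocation (sidedness and ratio assumed): n = [1.960·√(2 × 0.067 × 0.933) + 1.282·√(0.10 × 0.90 + 0.034 × 0.966)]² / 0.066² ≈ 300 per arm, 600 in total. It does not bear on recurrence.

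**Inputs from the article.** Accrual from 6 February 2017 to December 2019; data collection to June 2020; last visit at 2 years; 20% loss; 720 patients.

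**Assumptions.** Uniform accrual; constant recurrence hazard; true 2-year risk p of 2% to 5%; loss spread evenly over 0 to 2 years.

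**Step 1: who can reach 2 years.** Only month names are given for the two end dates, so three readings were tried.

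| Last operation / data cut-off | Can reach 2 years | 1 to 2 years | Under 1 year | Mean follow-up (capped at 2 years) |
|---|---|---|---|---|
| 31 Dec 2019 / 30 Jun 2020 | 509/1,058 days = 48.1% (346) | 34.5% | 17.4% | 1.61 years |
| 1 Dec 2019 / 1 Jun 2020 | 480/1,028 days = 46.7% (336) | 35.5% | 17.8% | 1.60 years |
| 31 Dec 2019 / 1 Jun 2020 | 480/1,058 days = 45.4% (327) | 34.5% | 20.1% | 1.57 years |

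For the first row, mean follow-up = 0.481 × 2 + 0.519 × (2 + 0.498)/2 = 1.61 years.

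**Step 2: all randomised patients in the denominator.** With λ = −ln(1 − p)/2, the crude proportion is the mean of 1 − exp(−λt) over patients. For small p, its ratio to p is close to mean follow-up divided by 2: 1.57/2 = 0.78 to 1.61/2 = 0.81. The full calculation gives 0.79 to 0.81, so a true 2% reads about 1.6% and a true 5% reads 3.9% to 4.0%. The understatement is 19% to 21% relative.

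**Step 3: loss.** If everyone else were followed to 2 years and only the 20% loss applied, the ratio is (0.8 × 2 + 0.2 × 1)/2 = 0.90. Loss on top of the calendar gives 0.72 to 0.74.

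**Step 4: patients with at least 1 year.** In the first row, 0.481/0.826 = 58.2% of this set reach 2 years and the rest average 1.5 years. The ratio is (0.582 × 2 + 0.418 × 1.5)/2 = 0.90; across the three readings it is 0.89 to 0.90.

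**Step 5: only patients who reach the 2-year visit.** There is no deficit if censoring is non-informative, but events are thrown away. At p = 2% and before any loss, the first row gives 720 × 0.0161 = 11.6 expected recurrences, of which 346 × 0.02 = 6.9 fall in this set. About 40% of observed recurrences are discarded.

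**Step 6: early complications.** If 95% of events occur within 3 months (assumed), the ratio is 0.95 + 0.05 × (1.61 − 0.25)/1.75 = 0.99.

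**Step 7: comparison between arms.** With the same follow-up pattern in both arms, each rate shrinks by nearly the same factor. At 0.8, assumed true risks of 4% and 2% read about 3.2% and 1.6%. The difference falls from 2.0 to 1.6 points and its direction is unchanged.

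**The case against.** - **The denominator is not stated.** A reader might infer that the plan puts unobserved time into the 2-year denominator. The text does not go that far. Outcomes are set at discrete visits, and a test at each visit among those assessed there is an ordinary reading. The exception for patients lost to follow-up also points away from counting them as event-free. This stands, and the size is therefore conditional. But the two sets that the article names, intention to treat and 1-year complete cases, both admit patients not observed to 2 years, and the per-visit reading loses information (step 5).
- **The research period of 1 to 2 years.** A reader might take this to mean that many patients stop at 1 year; half doing so would give a deficit of about 25%. The documents do not support that, since every patient is scheduled for a 2-year visit.
- **The calendar conflict is a separate defect.** True, and if the study runs to the last participant's last visit, most of the inequality goes. The expected 20% loss would remain.
- **The effect is small beside sampling error.** At 4% with 300 per arm, the 95% interval is about ±1.96·√(0.04 × 0.96/300) = ±2.2 points, against a deficit of 0.4 to 0.8 points (10% to 20% of 4%). This stands, and recurrence is a secondary outcome.
- **Details belong in an analysis plan.** Denominators and censoring commonly do. The choice of test, however, is fixed in the article.
- **Sparse events.** At 2% to 4% of 720 there would be 14 to 29 recurrences, or 1.6 to 3.2 per centre over nine centres. A centre-stratified test may be too thin.

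**Conclusion.** The point holds for hernia recurrence and for other late-accruing, dated events. The stated crude-incidence test does not suit an outcome that runs to 2 years when, on the article's own dates and uniform accrual, fewer than half of patients could reach 2 years.

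The size depends on the unstated denominator: about 20% relative understatement with all randomised patients, about 10% if only the 20% loss applies, and about 10% among 1-year complete cases. These figures rest on uniform accrual, a constant hazard and assumed risks.

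Two stronger readings are not supported. First, not every 2-year complication is materially understated: for early events such as wound infection, haematoma and seroma the change is about 1% if they cluster in the first months. Second, the documents give no sign that follow-up will differ by arm, so the comparison should be read as diluted, not as biased in direction. Differential follow-up would change that. This is a worthwhile, inexpensive improvement to a secondary analysis.

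**What to change.** In the statistical analysis section:

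- Analyse hernia recurrence as time from surgery to first recurrence, using the recorded date, with patients free of recurrence censored at last contact.
- Report Kaplan-Meier estimates, or cumulative incidence with death as a competing event, at 1 and 2 years by arm, with a 95% confidence interval for the difference.
- Compare arms by a log-rank test, stratified by centre only if events are not too sparse.
- Keep chi-square or Fisher's exact test for complications up to 3 months.
- State the denominator for any proportion reported at 1 or 2 years.

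Reconcile follow-up length and data cut-off across the abstract, the AE reporting section, the completion/withdrawal section, the recruitment dates at the end of the ethical approval section, and the study completion section.

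The analysis change costs wording only. Aligning the cut-off may move the end date: 2 years after a December 2019 operation is December 2021. There are two limits. A recurrence found only at a yearly call may carry an approximate date, and censoring-based estimates are themselves biased if loss is related to recurrence.

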#### Other outcome measures.

Quality of life is evaluated by the SF-36.^21^The SF-36 is a 36-item, patient-reported survey of patient health. It consists of eight scaled scores, including vitality, physical functioning, bodily pain, general health perceptions, physical functioning, emotional functioning, social functioning and mental health. The score of each scale is summed and then standardised according to the formula: standardised score = (actual raw score—lowest possible raw score)/possible raw score range×100. The total SF-36 score is the standardised score based on the sum of the eight scaled scores. A higher score indicates better quality of life.

The cost utility analysis of therapeutic regimens involving different surgical approaches will be analysed. Medical costs consist of direct medical and non-medical costs. The direct medical costs include drug charges, inspection fees, laboratory fees, treatment fees, nursing fees and bed charges. The direct medical costs during hospitalisation will be calculated according to the hospital information system. Direct medical costs during the follow-up period will be reported by patients and/or their relatives. Direct non-medical costs include payments for transportation to receive medical care, cost of nutritional supplementation and the costs for accompanying family members during the treatment period.

All outcome evaluations will be independently performed by an experienced assessor blinded to the treatment regimens. The schedule of outcome measurement assessment is shown in table 3.

**Table 3 T3:** Timing of outcome measurement assessment

	Before surgery	During surgery	Follow-up				
	Visit 1 (at admission, day 0)	Visit 2 (at discharge)	Visit 3 (1 week after surgery)	Visit 4 (1 month after surgery)	Visit 5 (3 months after surgery)	Visit 6 (1 year after surgery)	Visit 7 (3 years after surgery)
Signed informed consent	X						
Inclusion/exclusion criteria	X						
Demographic data	X						
Medical insurance type	X						
Delayed visit and admission	X						
Previous history of diseases	X						
Previous history of drug	X						
Risk factors	X						
Disease attack and admission *	X						
Type of hernia (indirect hernia, direct hernia)	X						
Vital sign†	X						
Laboratory examination ‡	X	X					
Imaging examination §	X						
Electrocardiography	X						
Treatment regimen ¶		X					
VAS score **						X	X
SF-36 score			X	X	X	X	X
Medical cost		X	X	X	X	X	X
Concomitant treatment	X	X					

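### SF-36 is measured at five postoperative visits with 20% loss expected, but is assigned a two-sample test that makes no use of earlier scores (minor)

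*Protocol article*

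**What the plan says.** The Statistical analysis section gives one sentence for continuous variables, with SF-36 as its only example: "Independent sample t-test or Mann-Whitney U test will be used for comparisons of continuous variables, such as SF-36 score, between groups". It gives no rule for choosing between the two tests, and it puts the whole analysis under the intention-to-treat principle. The next sentence treats economics separately: "Cost-utility analysis will be used for economic evaluation, and sensitivity analysis of cost and utility will be performed".

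Under Other outcome measures, "Quality of life is evaluated by the SF-36". The Follow-up section lists the SF-36 at 1 week, 1 month, 3 months, 1 year and 2 years. The last entry reads "Visit 7 (2 years after surgery via telephone follow-up)VAS pain score;SF-36 score;Medical costs", and the 1-year and 2-year visits are by telephone only. Table 3 marks the same five visits, although it labels the last one 3 years. Neither place shows a preoperative SF-36.

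On loss, the Sample size section says "Assuming a patient loss rate of 20%, we require 720 patients". The section on patient completion and withdrawal says that last-visit data will be evaluated, but not for patients lost to follow-up.

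**The concern.** A two-sample test takes one value per patient. Applied at 1 or 2 years, it uses only patients seen at that visit. Someone who answered the SF-36 at 1 week, 1 month and 3 months and was then lost adds nothing to the 2-year comparison. That fits poorly with an intention-to-treat analysis.

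Two things are at stake. First, if patients with poor scores are more likely to be lost, and more so after one approach than the other, the late comparison is biased even when the approaches are equivalent. Second, collected data are wasted. In addition, with five visits and no main one, the result to be read as the quality-of-life finding is open.

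This is more than a missing detail, because the article names the test. An analysis plan that follows the article would inherit it.

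**Working it through.** **Step 1. The plan's own figure.** The only computed design figure is the sample size for the primary outcome, 10% versus 3.4%, α = 0.05, power 90%. Two-sided, with pooled variance under the null:

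n per arm = [1.960·√(2·0.067·0.933) + 1.282·√(0.10·0.90 + 0.034·0.966)]² / 0.066² = (0.693 + 0.449)² / 0.004356 ≈ 299.5, so 300 per arm and 600 in total.

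The stated 600 is reproduced, and 600 × 1.2 = 720. The present point does not dispute this figure; no power statement rests on SF-36. A 20% loss from 720 is 144 patients, which leaves 576, or 288 per arm.

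**Step 2. Bias of an available-case comparison.** Assumed inputs, none from the documents: SD 10, equal correlation ρ between visits, no true difference, 360 per arm. About 20% are missing at the last visit in each arm. In one arm loss depends on the previous score through a probit rule; in the other it is random.

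- The rule is: lost with probability Φ(−Z − 1.19), where Z is the standardised previous score. The average loss is Φ(−1.19/√2) = Φ(−0.841) = 0.20.
- Mean of Z among those who stay: (1/√2) × φ(0.841)/Φ(0.841) = 0.707 × 0.280/0.80 = 0.2475.
- Bias at the last visit = SD × ρ × 0.2475: 1.24 points at ρ = 0.5 and 1.73 at ρ = 0.7.
- Simulation of 1000 trials gave 1.25 and 1.73. Predicting the last score from the four earlier ones for every patient gave −0.02 and 0.00.

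For scale, the standard error of the difference at 288 per arm is about 10·√(2/288) = 0.83. The bias is thus about 1.5 to 2.1 standard errors. If the same rule applied in both arms, the two shifts would cancel and the bias would be 0.

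**Step 3. Precision.** Consider the 2-year mean with the 1-year score as auxiliary information.

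- All patients missing at 2 years were seen at 1 year: variance ratio 1 − 0.20ρ² = 0.95 (ρ = 0.5) or 0.90 (ρ = 0.7). The reduction is 5% to 10%, and the interval is about 2.5% to 5% narrower.
- Half of the loss occurs before 1 year, so 90% are seen at 1 year and 80% at 2 years: ratio 1 − ρ²(1 − 80/90) = 0.97 or 0.95. The reduction is about 3% to 5%.

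**Step 4. No main visit.** If each of the five visits were tested at 0.05 without adjustment, the chance of at least one false positive would be 1 − 0.95⁵ = 22.6% under independence. By simulation it is 18.2% at a between-visit correlation of 0.5 and 14.9% at 0.7. The article does not say that five tests will be run; this only shows why one visit should be named.

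**Step 5. Costs, only if compared between arms outside the cost-utility analysis.** Assumed log-normal costs, 288 per arm, log-SD 0.5 versus 0.8. With equal means, Mann-Whitney rejects in 93% of trials and the Welch t-test in 6%. With equal medians and means 22% apart, Mann-Whitney rejects in 6% and the t-test in 84%. Ranks do not follow the arithmetic mean; the t-test does.

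**The case against.** The case on the other side has five parts.

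- **A t-test at one visit is not invalid.** If loss is completely at random, or depends on scores equally in both arms with no true difference, the contrast is unbiased. This stands. The bias in Step 2 needs loss that depends on scores and differs by arm, and its size comes from assumed inputs. The 20% is a planning figure for the whole trial, not a stated rate of missing SF-36.
- **The efficiency gain is small.** This also stands: 5–10% is a ceiling. A larger gain could be had by averaging the 1-year and 2-year scores. That answers a different question, and a t-test on each patient's average would do it too, so it is no argument against the stated test.
- **Such detail belongs in the analysis plan.** This holds for the covariance structure and the missing-data model. It does not remove the point, because the article states a method, and that method does not fit the data collected.
- **These outcomes are peripheral.** SF-36 and costs are listed as other outcomes. The Discussion calls quality of life and cost-utility secondary, so they carry some weight, but the primary outcome is binary and has its own test.
- **Costs are handled elsewhere.** A reader might infer that skewed costs will go to Mann-Whitney and could contradict the economic evaluation. The documents do not support this. The sentence names only SF-36, cost and utility have their own sentence, no rule links skewness to a rank test, skewness is not mentioned, and the t-test option compares means. What remains is a conditional remark: the phrase covering continuous variables is open-ended and does not exclude costs.

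**Conclusion.** The point holds for SF-36, at minor severity. The named test uses neither the five-visit structure nor the earlier scores of patients who are later lost. The possible harm is a bias of about 1.3 to 1.7 points at the last visit, assuming SD 10, correlations of 0.5 to 0.7 and score-dependent loss of about 20% in one arm only. It is nil if loss is unrelated to scores. The cost in precision is at most 5–10% of the variance at 2 years, and less if loss comes before 1 year.

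The documents do not support the stronger readings that every continuous outcome is mishandled, that costs will be tested by ranks, or that the SF-36 test is invalid in itself. The primary analysis and the sample size are not touched.

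**What to change.** Replace the SF-36 test with one linear mixed model on all five postoperative visits. Include arm, visit, arm-by-visit interaction and centre, with an unstructured covariance, and every randomised patient with at least one score. Name one visit contrast as the main one and treat the others as supportive. Because Follow-up and Table 3 date the last visit differently, settle that date before choosing it.

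For costs, add one conditional sentence: any comparison between arms outside the cost-utility analysis uses the difference in arithmetic means with a bootstrap interval, not ranks.

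The cost is a change of wording and slightly more programming in standard software; no new data are needed. The drawback is that the model relies on loss being at random given the observed scores. That is weaker than the completely-at-random condition under which the stated test is generally unbiased, but the data cannot prove it.
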